### Study intervention

Patients will be randomised after a diagnosis of resectable stage III melanoma to receiving either two cycles of intravenous infusion with ipilimumab 80 mg plus nivolumab 240 mg (combination therapy administered at 3-weeks interval) or two cycles of intravenous infusion with nivolumab 480 mg (monotherapy administered at 4-weeks interval) (Figure 1). In both groups, the two neoadjuvant treatment courses will be followed by an index node resection (in patients with lymph node metastases) or radical surgery for in-transit metastases. Patients with MPR, receive no further treatment and will enter follow-up. In the absence of MPR, patients with lymph node metastases undergo TLND and then receive adjuvant treatment, nivolumab 480 mg (Q4w x12), or if harbouring BRAF V600E tumour mutation, 46 weeks of dabrafenib 150 mg x2 and trametinib 2 mg 1×1.

**Figure 1 F0001:**
[figure not shown]
Trial overview. ICI: Immune checkpoint inhibitors. IPI: Ipilimumab, NIVO: Nivolumab, MPR: Major pathological response, LN: Lymph node. *Up to three resectable in-transit metastases are permitted, where included patients are stratified according to the presence or absence of in-transit metastases.

### Study design

The study is a phase III superiority trial comparing neoadjuvant anti-PD-1 monotherapy to anti-CTLA-4/anti-PD-1 combination therapy in patients with resectable stage III–IV melanoma with EFS as the primary endpoint. The sample size and power calculations are based on a two-sided type 1 error of 5% and a statistical power of 70%. A power of 70% was selected as a deliberate balance between the risk of a false-negative conclusion and the feasibility constraints imposed by a limited recruitable population and event accrual within a reasonable study timeframe. Included patients are stratified according to the presence or absence of in-transit metastasis. Randomisation is 1:1 with a total sample size of 128 subjects (64 per arm), with a total number of 85 events required to detect a difference in EFS of 13% or higher between the two groups. This is based on indirect cross-trial comparison of 24-month EFS rates between neoadjuvant pembrolizumab in SWOG S1801 (EFS 72% at 24 months) and neoadjuvant ipilimumab+nivolumab in NADINA (EFS 77% at 24 months). However, this cross-trial difference is expected to underestimate the true regimen effect due to differences in patient populations, perioperative systemic therapy exposure, and follow-up structures. On this basis, SWE-NEO prespecifies a clinically meaningful absolute EFS difference of 13%, representing a benefit magnitude that would justify the additional toxicity of the added CTLA-4 blockade and remains conservative relative to the ~20–25% absolute EFS gains observed when neoadjuvant strategies are compared with adjuvant-only approaches. Included patients are stratified for in-transit metastases. The anticipated accrual time is 2 years, and the follow-up period is 5 years.

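### The 85 required EFS events do not follow from the cited 72% monotherapy EFS and a 13-point gain at 70% power; the rates behind 85 must be stated and reconciled

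*Protocol article*

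**What the plan says.** All the figures are in the Study design section of the protocol article.

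- Error rates: "a two-sided type 1 error of 5% and a statistical power of 70" per cent. The power level is defended explicitly: "A power of 70% was selected as a deliberate balance between the risk of a false-negative conclusion and the feasibility constraints".
- Size: "Randomisation is 1:1 with a total sample size of 128 subjects (64 per arm").
- Event target and effect: "with a total number of 85 events required to detect a difference in EFS of 13% or higher between the two groups".
- Evidence base, named in the next sentence: "neoadjuvant pembrolizumab in SWOG S1801 (EFS 72% at 24 months") and "neoadjuvant ipilimumab+nivolumab in NADINA (EFS 77% at 24 months").
- The observed 5-point gap is then said to be too small a guide to the true effect, and "SWE-NEO prespecifies a clinically meaningful absolute EFS difference of 13" points.
- Accrual is planned over 2 years and follow-up over 5 years.

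The section gives no hazard ratio, no rate labelled as the planning control rate, and no time point for the 13-point difference.

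**The concern.** The number of events for a log-rank comparison depends on the hazard ratio. A 13-point difference fixes a hazard ratio only once the control rate is known. Monotherapy is the comparator, and 72% is the only monotherapy EFS rate in the article. It appears directly after the event target as part of its basis, so a reader will naturally take 72% as the control rate and 85% as the target. That pair does not lead to 85 events at the stated power.

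The event count sets the information available for the primary comparison. As the text stands, a reader cannot tell which effect has 70% power, or whether 128 patients can produce the required events.

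**Working it through.** **Inputs (Study design).** Two-sided alpha 5%, power 70%, allocation 1:1, N = 128, 85 events, 13-point difference, cited 24-month EFS 72% and 77%, accrual 2 years, follow-up 5 years. Assumption: proportional hazards.

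**Formulas.**
- HR = ln(S_exp) / ln(S_ctrl)
- Schoenfeld events = 4(z_α + z_β)² / (ln HR)²
- Freedman events = (z_α + z_β)² × [(1 + HR)/(1 − HR)]²
- Power with d events = Φ(|ln HR| × √d / 2 − 1.960)

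For 70% power, (1.960 + 0.524)² = 6.172.

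**1. Reproducing 85 from the cited monotherapy rate.** For 72% versus 85%, HR = (−0.1625)/(−0.3285) = 0.495 and ln HR = −0.704.
- Schoenfeld: 4 × 6.172 / 0.704² = 49.8.
- Freedman: 54.0.
- Power with 85 events: Φ(0.704 × √85 / 2 − 1.960) = Φ(1.284) = 0.900.

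So 85 is not reproduced. It is about 1.7 times the Schoenfeld figure.

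**2. What does reproduce 85.**

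| Pair | HR | Power | Schoenfeld events | Freedman events |
|---|---|---|---|---|
| 72% vs 85% | 0.495 | 70% | 49.8 | 54.0 |
| 64% vs 77% | 0.586 | 70% | 86.2 | 90.4 |
| 72% vs 85% | 0.495 | 90% | 84.9 | 92.0 |
| 72% vs 77% (the cited pair) | 0.796 | 70% | 472 | 476 |

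At 70% power, 85 events correspond to HR 0.583 (Schoenfeld) or 0.575 (Freedman). With a 13-point gain, that means a control rate of about 64% or 65% respectively. The equation also has a root near 5%, which is of no practical interest here. With 64% versus 77%, 85 events give power Φ(0.535 × √85 / 2 − 1.960) = 0.694.

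**3. A test of two proportions** does not explain the design. At 70% power, 72% versus 85% needs 123 per arm (138 with continuity correction), against 64 planned.

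**4. Events that 128 patients can supply.** Assumptions: exponential EFS matching the 24-month rates, uniform entry over 2 years, no dropout. Expected events per arm = 64 × [1 − mean of S^(t/2)], with t the patient's follow-up in years. With 5 years after the last entry, t runs uniformly from 5 to 7.
- 72% vs 85%: 64 × (1 − 0.375) + 64 × (1 − 0.615) = 40.0 + 24.7 = about 65 events, power about 81%.
- 64% vs 77%: 64 × (1 − 0.264) + 64 × (1 − 0.458) = 47.1 + 34.7 = about 82 events, power about 68%.

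If the 5 years are instead counted from the first entry (t from 3 to 5), the totals are about 48 and 64.

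**The case against.** The best defence is that the article never calls 72% the planning control rate. It describes an indirect comparison of two trials and says this understates the effect. Under Perspectives it adds that only the combination trial used the response-adapted approach, which blurs the comparison. Subtracting 13 from the cited 77% gives 64%. At the stated alpha and power, 64% versus 77% needs 86 events, within about 1.5% of 85. On that reading difference, events, alpha and power agree. This stands, and it rules out saying that the stated figures certainly cannot all hold, or that the cited evidence base is wrong.

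A reader might also infer that 85 can arise only from a 64% control rate. That is true only at 70% power. 72% versus 85% at 90% power gives 84.9, so the discrepancy could lie in the stated power instead, although the explicit defence of 70% speaks against that. The time point is open too: under exponential EFS, 72% at 24 months is 64.5% at 32 months, and a 13-point gain there needs about 84 events. Nothing shows that this route was used.

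Finally, the article condenses a full protocol in the Supplementary Material, which may give the rates. Their absence alone would be no finding. The point that remains is that the article itself prints an event count, a difference, a power and an evidence base, and their natural reading does not give 85.

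**Conclusion.** The concern holds in limited form. If the cited 72% is the control rate, a 13-point gain needs about 50 to 54 events at 70% power, and 85 events would correspond to about 90%. If 70% power is right and the difference is 13 points, 85 events require a control rate of about 64 to 65%, which is unstated and about 8 points below the cited monotherapy rate. The document does not show which applies.

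The two readings differ in what the trial can deliver. With 5 years after the last entry, 72% versus 85% yields about 65 events and never reaches 85, while 64% versus 77% yields about 82, close to the target.

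Neither reading shows a seriously underpowered test for its own 13-point effect when follow-up runs 5 years after the last entry, and neither affects the type I error. The required-events figures rest on proportional hazards. The expected-events figures also rest on exponential EFS, uniform 2-year accrual and no dropout.

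**What to change.** In Study design, and wherever the full protocol and SAP repeat the calculation, state the planned 24-month EFS in each arm, the hazard ratio and the time point at which the 13 points apply. Make the event count and power agree with them, with N unchanged at 128. There are two consistent ways to do this:

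- (a) Declare 72% versus 85%, HR 0.495, and restate the requirement as about 50 to 54 events for 70% power. Do not claim 90% power at 85 events, because 128 patients would not supply 85 events under these rates.
- (b) Declare that planning used about 64% versus 77%, HR about 0.586, with about 86 events. Justify the 64% control rate, and stop presenting 72% as the basis.

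In either case, print the expected number of events from 128 patients beside the required number, and say when the 5-year follow-up clock starts. Under (a), about 65 events are expected with 5 years after the last entry, but about 48 if the 5 years run from the first entry.

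The cost is a few sentences and one recalculation, with no extra patients. All three sites were enrolling as of December 2025 (Trial status), so this should be settled and dated before outcome data could influence the choice.

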### Endpoints

The primary endpoint is EFS, defined as time from randomisation to melanoma progression (unresectable stage III or stage IV disease), melanoma recurrence, or death from any cause (treatment-related, melanoma related or any other).

The secondary endpoints of the SWE-NEO trial are:

RFS, defined as the time from the date of surgery to the date of melanoma recurrence, treatment-related death or melanoma-related death, whichever occurs first.Distant metastasis-free survival (DMFS), defined as the time from the date of randomisation to the date of first distant metastasis, treatment-related death or melanoma-related death, whichever occurs first.OS, defined as time from the date of randomisation to the date of death from any cause.MPR, defined as ≤10% viable tumour cells in the excised tumour.Correlation of pathologic response in each arm to RFS, DMFS, and OS.Correlation of radiological and clinical response evaluation to RFS, DMFS, and OS.Proportion of patients having surgery according to protocol-defined timing (within 10 weeks from first neoadjuvant treatment course).Surgical complication rates graded according to Clavien-Dindo surgical classification.Frequency and duration of all grade and grade 3–5 treatment- related adverse events (AEs), graded according to Common Terminology Criteria for Adverse Events (CTCAE) 5.0.

Explorative endpoints include different biological markers analysed from sequential blood and tumour samples and their correlation with treatment efficacy and safety. The following will be studied as potential biomarkers:

Circulating tumour DNA (ctDNA) in plasma.Extracellular vesicles (EVs) in plasma.Multiparameter flow cytometry, and to profile immune cells in peripheral blood mononuclear cells (PBMC) isolated from blood.Single cell analyses of tumour and blood samples including single cell RNA sequencing and T cell and B cell receptor profiling to determine predictive biomarkers.Tumour spatial transcriptomic analyses to determine tumour architectural features that associate with pathological response and EFS.

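### The cited 24-month EFS rates do not yield 85 events from 128 patients in the stated timeline, and the control rate behind the 85 is not stated

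*Protocol article*

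**What the plan says.** All the design figures stand in one paragraph of the protocol article, under Study design.

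- Error rates: "two-sided type 1 error of 5% and a statistical power of 70" per cent.
- Size: "Randomisation is 1:1 with a total sample size of 128 subjects (64 per arm").
- Events: "with a total number of 85 events required to detect a difference in EFS of 13% or higher between the two groups".
- Rates given as the basis: "neoadjuvant pembrolizumab in SWOG S1801 (EFS 72% at 24 months") and "neoadjuvant ipilimumab+nivolumab in NADINA (EFS 77% at 24 months").
- Effect: the article expects the 5-point cross-trial gap to understate the true effect, and so "SWE-NEO prespecifies a clinically meaningful absolute EFS difference of 13" per cent.
- Timeline: "The anticipated accrual time is 2 years, and the follow-up period is 5 years".

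Under Endpoints, EFS is "defined as time from randomisation to melanoma progression (unresectable stage III or stage IV disease), melanoma recurrence, or death from any cause", so deaths from other causes count as events.

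The article does not give the control-arm rate or hazard ratio from which the 85 was calculated. It does not say whether the 5 years runs per patient or from the last randomisation. It justifies 70% power partly by the events that can accrue in a reasonable time.

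**The concern.** Reaching 85 events in 128 patients means that 85/128 = 66.4% have an event. The two cited rates leave 72% and 77% of patients event-free at 24 months, so most of the required events would have to come later. Whether they can depends on the rates assumed and on how long patients are followed.

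The stated 70% power is tied to the 85 events. If the rates, the event target and the timeline do not belong to one calculation, a reader cannot tell what power the trial will have when follow-up ends, or whether 85 is the right number to aim for. Because event accrual is part of the reason given for accepting 70% power, the mismatch also touches the argument for the design.

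**Working it through.** **Inputs (Study design).** Two-sided 5%, power 70%, 64 patients per arm, 85 events, 24-month EFS of 72% and 77%, difference of 13 points, accrual 2 years, follow-up 5 years.

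**Assumptions (not in the article).** Constant hazard, uniform accrual, no dropout.

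**Step 1: reproduce the 85.** The Schoenfeld formula for 1:1 allocation is d = 4(1.960 + 0.524)² / (ln HR)² = 24.69 / (ln HR)², with HR = ln(S_combination) / ln(S_mono) at 24 months. Solving for d = 85 gives HR = 0.583.

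| 24-month EFS, mono vs combination | HR | Events for 70% power |
|---|---|---|
| 72% vs 77% (both cited) | 0.796 | 473 |
| 72% vs 85% (72 + 13) | 0.495 | 50 |
| 64% vs 77% (77 − 13) | 0.586 | 87 |
| 59% vs 72% (72 as the combination rate) | 0.623 | 110 |

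Of the three pairs that are 13 points apart and use a cited rate, only 64% vs 77% comes close to 85. At 85 events its power is 69.4%. (The Freedman formula gives 55 events for 72% vs 85% and 91 for 64% vs 77%.)

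**Step 2: expected events.** With λ = −ln(S24)/2, the probability of an event is:

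- 5 years after the last randomisation (analysis at year 7): P = 1 − (e^(−5λ) − e^(−7λ)) / (2λ)
- exactly 5 years per patient: P = 1 − e^(−5λ)

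Example for 72%: λ = 0.1643, so P = 1 − (0.4399 − 0.3167)/0.3285 = 0.625, and 64 × 0.625 = 40.0 events. For 77%: λ = 0.1307, P = 0.542, and 34.7 events. The sum is 74.7.

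| Pair | Events at year 7 | Events at 5 years per patient | Years after last patient at which 85 is expected |
|---|---|---|---|
| 72% vs 77% | 74.7 | 66.6 | 6.5 |
| 72% vs 85% | 64.7 | 57.2 | 8.5 |
| 72% in both arms | 80.0 | 71.7 | 5.7 |
| 64% vs 77% | 81.8 | 73.7 | 5.4 |

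Even if every patient had the worse of the two cited rates, 85 events would not be expected on either reading of the 5 years.

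**Step 3: power at those counts.** Power = Φ(|ln HR| √d / 2 − 1.960).

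| Pair | Year 7 | 5 years per patient |
|---|---|---|
| 64% vs 77% | 68% | 63% |
| 72% vs 85% | 81% | 76% |
| 72% vs 77% | 17% | 15% |

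**Sensitivity.** The article gives only 24-month rates, so the later hazard is unknown. If it halved after year 2, the year-7 counts would be 56.8 (72% vs 77%), 48.5 (72% vs 85%) and 63.8 (64% vs 77%). Dropout would lower them too. A hazard that rises after 24 months would raise them.

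**The case against.** The strongest reply is that 72% vs 77% is not the design pair. The article says that the cross-trial gap understates the effect and then sets 13 points, and 85% is printed nowhere. On 64% vs 77%, the pair that roughly recovers the 85, the longer reading of follow-up gives about 82 events, 3 short of the target, with 85 expected about 5 months late and power of 68% against 70%. This stands: on that pair and reading, target and timeline nearly agree. What remains is that the pair needs a control rate of 64%, which the article does not state, while the only monotherapy rate that it gives is 72%. With 5 years per patient, the pair falls about 11 events short.

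A reader might infer that the trial will be underpowered whatever the rates, or that 85 events can never be reached. Neither follows. At 72% vs 85% about 50 events suffice, and the roughly 65 expected give about 81% power at constant hazard. At constant hazard every pair considered reaches 85 in expectation, though after planned follow-up. The low power at 72% vs 77% reflects the small effect: at 85 events it would still be only 18%.

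A reader might also infer that the primary analysis waits for 85 events. The article calls 85 the number required to detect the difference and does not say that the analysis is triggered by it. The trigger and a detailed event projection may properly sit in the full protocol or the SAP, and their absence here is not the point. The point is that the figures which the article does print do not fit one another.

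**Conclusion.** The point holds in this form: 85 events, 128 patients, the cited 24-month rates, and 2 years' accrual with 5 years' follow-up do not come from one consistent set of assumptions. At the cited rates the expected shortfall by year 7 is about 10 events (72% vs 77%) or 20 (72% vs 85%). With 5 years per patient it is about 18 or 28.

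Two explanations are possible, with different consequences. If the design pair is 64% vs 77%, the target is about right, but the control rate is undisclosed and lies 8 points below the cited 72%; power by the end of follow-up is about 68% or 63%, depending on how the 5 years is counted. If it is 72% vs 85%, the 85-event target is wrong for 70% power, and power is above 70% on both readings at constant hazard.

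The counts rest on constant hazard, uniform accrual and no dropout. The declining-hazard counts are sensitivity cases and do not carry the conclusion.

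**What to change.** 1. State the control-arm 24-month EFS and the hazard ratio behind the calculation. If the control rate is below 72%, say why.
2. Restate the required number of events so that it follows from those rates at two-sided 5% and the chosen power.
3. Say whether the 5 years of follow-up runs per patient or from the last randomisation.
4. Replace the statement of 85 events and 70% power with the events expected by the end of planned follow-up and the power that they give, at constant hazard and with a declining-hazard sensitivity.

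A calendar backstop for the primary analysis is one reasonable way to deal with a shortfall in events; others are possible.

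The cost is wording in the protocol and SAP, with no extra patients. The stated power may go down or up, depending on the rates adopted. All three sites are enrolling, so the change is best made now, before event data accumulate.

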### Ethical consideration

In resectable stage III melanoma, both neoadjuvant PD-1 inhibitor monotherapy and PD-1 and CTLA-4 inhibitor combination have been shown to result in improved EFS and DMFS compared to adjuvant-only treatment. As of December 2025, neither regimen has been approved by the EMA or the FDA. However, in Sweden, both these regimens have been approved for neoadjuvant treatment in resectable stage III melanoma. The PD-1/CTLA-4 inhibitor combination is potentially more effective, but also associated with increased toxicity and higher treatment costs. In patients presenting with resectable stage III melanoma, acceptance of the risk of serious, life-threatening, or chronic side effects is generally lower than in the setting of inoperable metastatic disease. Therefore, it is possible that PD-1 inhibitor monotherapy regimen is sufficient in this clinical setting. It is therefore essential to study this benefit/risk balance to determine which treatment strategy is most beneficial. In addition, translational analyses aim to identify biomarkers that may guide treatment selection for individual patients.

Patient representatives from the Swedish melanoma patient association (Melanomföreningen) were consulted during protocol development to ensure patient relevance and acceptability, and they expressed support for the final study design. The study will be conducted in accordance with Good Clinical Practice (GCP) guidelines and the Declaration of Helsinki. All participants will receive oral and written information regarding risks of participation and their right to withdraw from the study at any time. All participants are required to provide signed and dated written informed consent (available in the Supplementary Material) prior to participation. The trial protocol is reported in accordance with the SPIRIT guidelines for clinical trials (see Supplementary Material). The trial was approved on April 30th, 2025, by the EMA Clinical Trials Information System (CTIS) (trial ID: 2024-519593-39-00) and by the Swedish Biobank Authority. ClinicalTrials.gov identifier is NCT06794775, registered on January 22nd, 2025.

## Perspectives

SWE-NEO is a fully academic trial comparing two courses of either nivolumab monotherapy or nivolumab plus ipilimumab in the neoadjuvant setting. The feasibility of fully recruiting the trial within 2 years is based on the national experience with neoadjuvant treatment since its implementation in Sweden as clinical routine in 2022 [9]. The response adapted switch to BRAF/MEK inhibition in both arms will aid to give insights on the true effect on outcome comparing neoadjuvant combination or monotherapy, where such adaptive approach was only applied in NADINA and not in SWOG S1801, which obscures the comparison between these two studies. The results are expected to provide valuable insights to define the optimal neoadjuvant approach for resectable stage III melanoma. The results of the trial are expected to directly inform clinical decision-making by identifying the regimen that provides the best balance of efficacy and safety, potentially shaping future standard of care.

## Trial status

As of December 2025, the SWE-NEO trial is open at the three participating sites, in Stockholm (Karolinska University Hospital), Gothenburg (Sahlgrenska University Hospital) and Lund (Skåne University Hospital) and all sites have initiated patient enrolment. Further details on the SWE-NEO trial are provided in the study protocol in the Supplementary Material.

